#### Follow-up assessments T1, T2, and T3

The follow-up assessments take place every 6 (+ − 2) months. In each follow-up, all clinical data and prescription plans will be assessed. After ABPM and the following consultation focusing blood pressure protocol, patients are asked to complete a follow-up questionnaire which includes MARS, TPS, knowledge about hypertension, treatment decision made to control hypertension, SDM-Q-9, tobacco consumption, height and weight, and utilisation of further health services.

#### Incentives reliant on realisation of data assessment

The GP practices or medical assistants, respectively receive a case payment of 10 € per complete dataset of each patient in each assessment. The ABPM equipment will be offered to the GPs after the end of the study.

### Data management

All pseudonymised data of the patient questionnaires, forms, prescription plans, ABPM protocols and filled prescriptions will be merged into an SPSS data file. The quality of the data entry of each assessment will be proved by a 10% random sample check. Additionally, extensive plausibility checks are performed.

Major analyses will be conducted by the Clinical Trials Unit at the University Medical Centre Freiburg. Statistical programming will be performed with the Statistical Analysis System (SAS) Version 9.2 or higher.

### Sample size calculation

The sample size calculation resulted in about 40 practices (20 per intervention group) with a total of 1200 patients (600 per treatment group), including about 20% drop outs on patient as well as practice level. Hence, data on 788 patients are expected to be available for analysis (i.e. about 33 practices with 24 patients each). Studies regarding hypertension prevalence [3,29] assume that about 1/3 of recruited patients attain blood pressure control. Therefore 1800 patients should be involved into the baseline data assessment. Thereof 2/3 or 1200 patients respectively will remain in the study.

Due to changes in the statistical analysis plan, a power calculation for the new analysis strategy has been performed (see section ‘Power calculation for the analysis of primary endpoints’).

### Statistical analyses

#### Analysis principle

The analysis of the primary endpoints ‘change of perceived participation’ and ‘change of systolic blood pressure will be done according to the intention-to-treat (ITT) principle. As we have no means to define protocol violations on the patient level and there were made no attempts to assess compliance at the practice level, no per-protocol analyses are planned.

#### Investigation of missing pattern

Prior to the analysis, the missing patterns will be explored. Depending on the findings, strategies will be worked out to reduce missing values. Possible strategies are, for example, imputation or exclusion of single items with many missing values in questionnaires.

In addition, we will analyse the missing patterns with respect to frequency and association with patient characteristics, with outcome measurements at other time points and with treatment status. The overall aim is to provide arguments to justify the use of a mixed model analysis, which formally relies on the missing at random (MAR) assumption.

#### Analysis of primary and secondary endpoints

For illustration of the main trends, boxplots will be used to visualise the distribution of primary and secondary outcome measurements at baseline and follow-up measurements as well as changes from baseline. In addition, the changes in the primary outcomes SDM and systolic blood pressure are plotted for each patient separately to explore the individual course of measurements.

The analysis of effectiveness of the intervention on the primary endpoints ‘change of perceived participation’ and change of systolic blood pressure will be performed with a mixed effects model of type

(1)$$Y_{\mathrm{ijk}}=\mu +\lambda Y_{\mathrm{ijb}}+a_{i}+\beta_{k}I_{i}+\gamma_{\mathrm{ij}}+\delta_{k}\epsilon_{\mathrm{ijk}}$$

where index *i* specifies the practice, *j* the patients (*j* = *1,…, no. of study patients in the corresponding practice)* and *k* the time point (*k = 2, 3* for systolic blood pressure and *k = 1,2,3* for perceived participation). In addition, μ is the intercept, α_i_ the random practice effect, β_k_ the fixed effect of intervention at time point T_*k*_, γ_ij_ the random patient effect, δ_k_ the fixed effect for time point T_*k*_, λ the fixed effect of baseline measurement Y_*ijb*_ (with *b = 0* for perceived participation and *b = 1* for systolic blood pressure) and ϵ_ijk_ the error term.

This model accounts for the variation within and between the clusters (medical practices). The effect of intervention (β) will be tested based on the mean of estimated effects over the different follow-up time points, i.e. $\beta =\frac{1}{2}\left(\beta_{2}+\beta_{3}\right)$ for systolic blood pressure and $\beta =\frac{1}{3}\left((\beta_{1}+\beta_{2}+\beta_{3}\right)$ for perceived participation. To adjust for multiple testing of the (co-) primary endpoints, a Bonferroni correction of the (two-sided) significance level α =0.05 will be applied, resulting in α* = α/2 = 0.025.

According to the EMA points to consider adjustment for baseline covariates [30] in ‘change from baseline’ analyses, the baseline value of the respective endpoint will be adjusted for.

The secondary endpoints will be analysed analogously with significance level 5%. No adjustment for multiple testing will be used.

For the endpoints systolic and diastolic blood pressure, medication adherence report scale (MARS) and cardiovascular risk score (CVR) with baseline T1, a model with baseline T0 is also considered as a sensitivity analysis.

For the primary endpoints, an additional sensitivity analysis based on a model adjusted for the prognostic factors practice, age, gender, baseline values of cardiovascular risk and comorbidity, MARS, API, intention to treat hypertension, helping relationship in taking medication, knowledge about hypertension, TPS and an indicator for treatment outside medical practice (aggregated over the complete study period) is conducted.

As an exploratory analysis, the influence of the prognostic factors mentioned above on the primary endpoints at baseline will be investigated.

No interim analysis will be performed during the course of the study.

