### Study endpoints

Co-primary endpoints are (1) change of patients’ perceived participation (measured by SDM-Q-9) from T0 to T1, T2 and T3, evaluated by the mean effect over the three time points, and (2) change of systolic blood pressure (mean of 24 h), measured by ABPM [27], from T1 to T2 and T3, evaluated by the mean effect over the two follow-up time points. While the intervention may affect perceived participation directly at the first visit after intervention (T1), changes in blood pressure cannot be affected before the second visit (T2).

Secondary endpoints are (1) change of diastolic blood pressure (24 h mean), (2) change of knowledge score, (3) change of adherence, measured by MARS-D and the MPR, and (4) change of cardiovascular risk score (CVR), all evaluated by the mean effect over the two and three follow-up time points, respectively. While the intervention may affect knowledge directly after T0, the other secondary endpoints will be affected at T2 at the earliest.

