#### Power calculation for the analysis of primary endpoints

For the power calculation we assume that 788 patients are available for analysis with 24 patients per practice (i.e. about 33 practices) according to the original sample size calculation (see above, section ’sample size calculation’). Since Kerry and Bland [32] state that the intra-cluster correlation in studies where the intervention is aimed at changing the doctor’s behaviour may be larger than in other cluster-randomised studies, we calculate the power assuming an intra-cluster correlation (ICC) of 0.05 and 0.03 which leads to a variance inflation factor [33] of 2.15 and 1.69, respectively. Hence, the sample size 788 in the cluster-randomised trial would correspond to a sample size of 366 and 466 patients, respectively, in a study with individual randomisation.

Since knowledge on the expected effects for systolic blood pressure and perceived participation is rare, we base the calculation on the standardised effect size [34]. According to Machin and Campbell (2005) [35], a standardised effect size of 0.2 and 0.5 corresponds to a small and moderate effect of the intervention, respectively. Under the reasonable assumption of a standardised effect size of 0.3 or 0.35, a conservative estimate of the ICC (0.05) and a significance level of α = 2.5% for the test on either co-primary endpoint, i.e. a global significance level of 5%, the power is about 74% and 87%, respectively. To account for the uncertainty in both the effect size and ICC, we use several choices of these parameters to get an overview of possible settings. Depending on the specific parameter setting, the power varies between 37% and 100% as displayed in Table 1. 

**Table 1 T1:** Power of analysis of primary endpoints under different assumptions of the intra-cluster correlation coefficient (ICC) and the standardised effect size

**Standardised effect size**	0,20	0,25	0,30	0,35	0,40	0,50	0,20	0,25	0,30	0,35	0,40	0,50
**ICC**	0,05	0,05	0,05	0,05	0,05	0,05	0,03	0,03	0,03	0,03	0,03	0,03
**Power (in %)**	37,14	55,96	73,51	86,58	94,35	99,45	46,71	67,62	84,05	93,78	98,11	99,92

These calculations are based on the assumption of only one measurement per patient during follow-up. They can be considered as conservative for the situation of repeated measurements at T1, T2, and T3, since this gives additional information (s. Table 1).

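### Single-step Bonferroni for the two primary endpoints is valid, but Holm's step-down keeps the same 5% family-wise level with more power and no extra patients

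*Protocol article*

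**What the plan says.** Under *Study endpoints* the protocol article names two primary endpoints: "change of patients’ perceived participation (measured by SDM-Q-9) from T0 to T1, T2 and T3", and "change of systolic blood pressure (mean of 24 h), measured by ABPM", from T1 to T2 and T3. Each is judged by its mean effect over the follow-up times.

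Under *Analysis of primary and secondary endpoints* the multiplicity rule is: "To adjust for multiple testing of the (co-) primary endpoints, a Bonferroni correction of the (two-sided) significance level" of 0.05, "resulting in α* = α/2 = 0.025". *Power calculation for the analysis of primary endpoints* uses the same level, "a significance level of α = 2.5% for the test on either co-primary endpoint", and equates this with a global 5%.

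No step-down or other sequential rule is described, and no reason is given for the single-step form. Secondary endpoints are tested at 5% each without adjustment, so no part of the primary alpha is being held back for them.

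**The concern.** Once one primary hypothesis has been rejected at 0.025, only one remains in the family, and it could be tested at 0.05 without raising the family-wise error above 5%. Under the rule as written it is still tested at 0.025, a stricter level than any secondary endpoint faces.

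The matter has some weight here. The background and discussion sections present the trial as a test of whether training improves participation and also blood pressure control, so a positive result on both endpoints would be the most informative outcome. The plan's own power per endpoint is moderate at the smaller effect it calls reasonable: about 74% at d = 0.30 and ICC 0.05.

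**Working it through.** **Inputs.** The power section states: "we assume that 788 patients are available for analysis with 24 patients per practice (i.e. about 33 practices". It takes ICCs of 0.05 and 0.03, "which leads to a variance inflation factor [33] of 2.15 and 1.69, respectively". Effects are d = 0.30 or 0.35, practices are split about 1:1, and the two-sided level is 0.025. The correlation between the two test statistics is not given; 0 to 0.5 is assumed.

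**1. Reproduce the plan's figure.**
- Variance inflation at ICC 0.05: 1 + (24 − 1) × 0.05 = 2.15. Effective n = 788 / 2.15 = 366.5 (stated: 366).
- Mean of the test statistic at d = 0.30: 0.30 × √(366/4) = 2.870.
- Power at 0.025: a = Φ(2.870 − 2.241) = 73.5%. Table 1 gives 73.51%.
- At d = 0.35 the mean is 3.348 and a = 86.6%. Table 1 gives 86.58%.

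All twelve cells of Table 1 reproduce to within 0.01 points.

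**2. Power at 0.05.** b = Φ(2.870 − 1.960) = 81.85% at d = 0.30, and 91.74% at d = 0.35.

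**3. Holm with independent statistics and equal effects, d = 0.30.**
- Per endpoint: a + (b − a) × a = 0.7351 + 0.0834 × 0.7351 = 79.6%.
- Both endpoints: Bonferroni a² = 54.0%; Holm b² − (b − a)² = 0.6699 − 0.0070 = 66.3%.
- At least one endpoint: 1 − (1 − a)² = 93.0% under either procedure, because the first step is the same.

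**4. With correlation (bivariate normal, ICC 0.05, equal effects).**

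| d | Correlation | Per endpoint, Bonferroni → Holm | Both, Bonferroni → Holm | At least one (either procedure) |
|---|---|---|---|---|
| 0.30 | 0 | 73.5% → 79.6% | 54.0% → 66.3% | 93.0% |
| 0.30 | 0.5 | 73.5% → 78.6% | 60.1% → 70.3% | 86.9% |
| 0.35 | 0 | 86.6% → 91.1% | 75.0% → 83.9% | 98.2% |
| 0.35 | 0.5 | 86.6% → 90.3% | 78.1% → 85.4% | 95.1% |

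At ICC 0.03 and d = 0.30, per-endpoint power goes from 84.1% to 88.1–89.0%. Power for both goes from 70.7% to 80.5% at correlation 0.

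**5. Unequal effects (independence, d = 0.30 on the endpoint of interest).** The gain is (b − a) times the other endpoint's power at 0.025.
- If the other endpoint has no effect: 0.0834 × 0.025 = 0.2 points.
- If the other has d = 0.10, its power at 0.025 is about 10%, and the gain is 0.0834 × 0.10 = 0.8 points.

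**6. Error control.** In simulation (4 million draws, correlations 0 to 0.5), Holm's family-wise error under the global null equals Bonferroni's: 4.9% at correlation 0 and 4.6% at 0.5. With one endpoint truly affected it is 4.1% to 5.0%, against 2.5% for Bonferroni. The 5% level is kept.

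**The case against.** The strongest objection is that nothing here is wrong. The rule is pre-specified and valid, and the stated level and power agree with each other. Bonferroni also has a practical merit: its 97.5% intervals match its decisions exactly. Holm adds a rejection only when the second p-value lies between 0.025 and 0.05, and in those cases the 97.5% interval includes zero. All of this stands. It makes the point one of efficiency, and it means the change needs explicit wording on intervals.

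Three stronger readings are tempting and are not supported.

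- **That power rises from 73.5% to 82%.** Those figures are conditional on the other endpoint having been rejected, and hold only under independence. At a correlation of 0.5 the conditional figures are 60.1 / 73.5 = 81.8% for Bonferroni and 88.7% for Holm. The unconditional gain per endpoint is about 5 to 6 points at d = 0.30.
- **That the trial needs both endpoints to succeed.** In such a design no alpha split would be needed at all. The power section speaks of "for the test on either co-primary endpoint, i.e. a global significance level of 5%, the power is about 74% and 87%, respectively", and the research objectives list participation and blood pressure as separate questions, so the plan makes separate claims.
- **That the gain is assured.** The article says little is known about the expected effects. Equal effects are an assumption, and step 5 shows how little is gained when one endpoint barely responds.

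**Conclusion.** A worthwhile, low-cost improvement; the plan as written contains no error on this point. Holm dominates single-step Bonferroni in rejections at the same strong 5% level, and the plan reserves no alpha that would argue against passing it on. At ICC 0.05 and d = 0.30 to 0.35, Holm adds about 4 to 6 points of power per endpoint and about 7 to 12 points for showing both, without further recruitment. These sizes rest on the article's effective sample size, equal effects on both endpoints, the normal approximation that reproduces Table 1, and an assumed correlation of 0 to 0.5. The error guarantee rests on none of these effect-size or correlation assumptions.

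**What to change.** Replace the Bonferroni sentence in *Analysis of primary and secondary endpoints* with Holm: compare the smaller of the two p-values with 0.025 and, if it is significant, compare the other with 0.05. Align the wording on the level in the power section and carry the rule into the SAP. Table 1 can stay, described as a lower bound on power per endpoint.

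Base the claims on Holm-adjusted p-values compared with 0.05: 2 × p(smaller) for the first endpoint, and the larger of 2 × p(smaller) and p(larger) for the second. If 97.5% intervals are reported, state that they are conservative and need not match the step-down decision; for an endpoint rejected only at the second step they will include zero.

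The cost is a short amendment and no patients. Because it relaxes a threshold for a primary endpoint, and the analysis strategy has already been changed once (see *Sample size calculation*), it should be justified and dated before any outcome data are compared by arm.

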### Randomisation of the GP practices

As soon as the baseline assessment has been completed, GP practices will be randomised into intervention and control group. The randomisation will be performed by lot procedure. Thus, about half of the GPs will be assigned to the intervention and half of the GPs to the control group.

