#### Additional analyses

Further analyses will be performed: (1) Association of practice characteristics with practice specific treatment effects, (2) predictiveness of change in a) perceived participation and b) TPS on change in systolic blood pressure, (3) association between a) change in perceived participation and change in TPS and b) change in adherence and change in perceived participation and systolic blood pressure, (4) comparison of the MPR with patients’ self-assessed adherence (MARS).

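### The adjusted sensitivity model for both co-primary endpoints includes a covariate collected after randomisation (treatment outside the practice), so as specified it is not a clean check of the primary result

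*Protocol article*

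**What the plan says.** Under Analysis of primary and secondary endpoints, the primary model (1) has a fixed effect for the baseline value of the endpoint, time effects, a random patient effect, and "α_i_ the random practice effect, β_k_ the fixed effect of intervention at time point T_*k". The intervention effect "will be tested based on the mean of estimated effects over the different follow-up time points".

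The same section then adds, for the primary endpoints only, a sensitivity analysis using "a model adjusted for the prognostic factors practice, age, gender, baseline values of cardiovascular risk and comorbidity". The list continues with several questionnaire scores and ends with "an indicator for treatment outside medical practice (aggregated over the complete study period) is conducted". All of these are called prognostic factors. The next sentence plans to explore how the same factors relate to the primary endpoints at baseline.

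On timing, Randomisation of the GP practices says "As soon as the baseline assessment has been completed" and then "GP practices will be randomised into intervention and control group". Under Follow-up assessments T1, T2, and T3, the patient questionnaire ends with "SDM-Q-9, tobacco consumption, height and weight, and utilisation of further health services". The section Baseline assessment describes two questionnaires, and neither includes use of further health services.

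**The concern.** A covariate-adjusted sensitivity analysis is meant to show whether the primary estimate survives allowance for prognostic imbalance. It does this only if the covariates could not have been changed by the treatment. A variable accumulated over follow-up does not meet that condition, for three reasons.

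- **Mediation.** If the training changes whether patients use care elsewhere, and that care affects blood pressure or perceived participation, adjustment removes this part of the training's effect.
- **Selection.** If outside care also depends on unmeasured prognosis, comparing arms within levels of the indicator compares unlike patients, even when outside care itself does nothing.
- **Reverse order.** A patient whose pressure stays high may seek care elsewhere. The outcome then causes the covariate.

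A pathway is plausible from the plan's own Intervention section: the training introduces a table of options for lowering cardiovascular risk, and practices receive leaflets on activity, nutrition and smoking. If the sensitivity and primary results then differed, the reader could not tell whether the primary result was fragile or the adjustment had caused the difference. Agreement would be equally hard to interpret.

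**Working it through.** **1. Timing of each covariate.** The sensitivity model lists ten covariates besides practice and the outside-treatment indicator: age, gender, cardiovascular risk, comorbidity, MARS, API, intention to treat hypertension, helping relationship, knowledge and TPS. All ten are covered by the clinical data, socio-demographic data or first questionnaire described under Baseline assessment. The indicator is the only one spanning the whole study, and its apparent source (use of further health services) is scheduled only at T1 to T3. That this questionnaire item is the source is an inference, because the article does not link the two explicitly. The indicator's own definition is enough to show that it includes time after randomisation.

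**2. Order relative to the outcomes.** Follow-up visits are 6 (±2) months apart. Perceived participation is modelled at T1, T2 and T3, so an indicator running to T3 includes nominally 2 × 6 = 12 months after the T1 outcome. Systolic pressure is modelled at T2 and T3, so the indicator includes nominally 6 months after the T2 outcome.

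**3. The plan's own figures.** No figure is given for this sensitivity model, so the power table was checked to confirm that nothing there is touched.

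- Design effect at ICC 0.05: 1 + (24 − 1) × 0.05 = 2.15. Effective sample size: 788 / 2.15 = 366.5.
- Power at 0.30 SD, two-sided alpha 0.025: Φ(0.30 × √(366.5/4) − 2.241) = Φ(0.63) ≈ 73.57%, against 73.51% in Table 1.
- At 0.35 SD: 86.63%, against 86.58%. All twelve cells agree within 0.1 point.

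None of these inputs involves the sensitivity model.

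**4. Illustration of the bias (assumed inputs).** The setting was 33 practices of 24 patients, one outcome per patient, and total variance 1 apart from the indicator: practice 0.05, an unmeasured prognostic factor 0.5² = 0.25, residual 0.70. The direct training effect was 0.30 SD. Use of outside care in controls was about 30% (log-odds −0.85 at the average prognosis). Each setting used 1,500 simulated trials and compared arms with and without the indicator.

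| Shift in log-odds of outside care due to training | Outside care related to unmeasured prognosis (log-odds per SD) | Effect of outside care on outcome (SD) | Unadjusted | Adjusted |
|---|---|---|---|---|
| 0 | 1 | 0 | 0.295 | 0.295 |
| −0.5 | 1 | 0 | 0.301 | 0.337 |
| +0.5 | 1 | 0 | 0.299 | 0.258 |
| −1 | 1 | 0 | 0.299 | 0.366 |
| +1 | 1 | 0 | 0.302 | 0.219 |
| −1 | 0 | 0.3 | 0.249 | 0.298 |
| +1 | 0 | 0.3 | 0.372 | 0.301 |
| −1 | 1 | 0.3 | 0.251 | 0.365 |
| +1 | 1 | 0.3 | 0.358 | 0.214 |

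The first five rows show selection alone, the next two mediation alone, and the last two both. The distortion can go in either direction and is absent when the training does not shift the indicator. The outcome-to-covariate path was not simulated.

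**5. Practice as random or fixed.** Columns for 33 practices:

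- Systolic pressure, practice fixed: 33 practice + 1 time + 2 intervention-by-time = 36 columns, rank 35. The mean of the β_k is not estimable; only their difference is.
- Perceived participation, practice fixed: 33 + 2 + 3 = 38 columns, rank 37. Again the mean is not estimable.
- Practice random, as in model (1): 1 + 1 + 2 = 4 columns, rank 4, and 1 + 2 + 3 = 6 columns, rank 6. The mean is estimable in both.

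The baseline value was left out of this count. Including it would not restore estimability, because the dummies of the trained practices still sum to the sum of the intervention columns.

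**The case against.** The strongest reply is that this is one labelled sensitivity analysis. The primary model, its test, the split of alpha and the power do not depend on it. Bias also requires that outside care responds to the training or to the outcome, and the documents say nothing about whether it does. Care received elsewhere is moreover a plausible co-intervention that the investigators may reasonably want to examine. All of this stands. It limits the weight of the point and supports keeping the variable in an exploratory model. It does not make the variable suitable for a robustness check, because the absence of an effect on outside care cannot be assumed in advance.

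Three stronger readings are tempting and are not supported:

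- **That practice is aliased with the intervention, so the model returns no estimate.** This holds only if practice becomes a fixed factor. The article never says so, and its only stated model has practice as random. The natural reading is model (1) plus covariates. Listing practice again is unclear, but it is not a demonstrated error.
- **That the sensitivity analysis cannot check the primary result at all.** The other ten covariates are available at T0. With practice random and the indicator removed, the model is an ordinary adjusted check.
- **That "Association of practice characteristics with practice specific treatment effects" under Additional analyses commits the trial to something it cannot estimate.** Each practice is in one arm, so the phrase is loose. But no model is given, and it can be read as effect modification by practice characteristics across both arms.

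**Conclusion.** The point holds for the outside-treatment indicator. The article itself names as an adjustment covariate a variable that runs past randomisation and, for the earlier follow-up visits, past the outcome. The sensitivity model as written is therefore not a clean check of the primary result.

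The size of any bias cannot be derived from the documents, which give neither the frequency of outside care nor its relation to training or outcome. The simulated results show only that the direction is unpredictable and that a distortion of several hundredths of an SD is possible under moderate to large assumed shifts. They should not be read as a forecast, and they cannot be turned into mmHg because the article states no standard deviation for blood pressure.

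The status of practice is a clarification only. The co-primary analyses, the 0.025 significance level and the stated power are unaffected.

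**What to change.** Remove the outside-treatment indicator from the adjusted sensitivity model and report it by arm as a post-randomisation variable. If the investigators wish to model it, they should do so in a separate model labelled exploratory. Substituting a T0 measure does not appear possible, since none is listed at baseline. The indicator should also come out of the exploratory analysis of factors at baseline, where a study-period total is not yet known.

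Add one sentence saying that practice stays the random effect of model (1) in the sensitivity model.

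The cost is a change of wording, with no new data and no change to sample size. The one loss, an adjusted look at co-intervention, is kept by the exploratory model.

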### Intervention

GPs of the intervention group will take part in an evaluated SDM training [6]. The training programme will be adapted to the requirements of hypertension treatment in general practice. The training involves at least two of three training sessions, with each session lasting three hours. The programme includes the following elements: (1) Information on arterial hypertension (epidemiology, treatment, patient adherence etc.), (2) principles of physician-patient-communication and risk communication, (3) information on the SDM concept including the implementation of the steps of the SDM process [7,10], (4) integration of Motivational Interviewing to enhance the patients’ intrinsic motivation to change health behaviour [8,9], (5) introduction of a decision table listing various options to lower cardiovascular risk, and (6) use of case vignettes for role plays simulating physician-patient consultations.

After the SDM training, GP practices will receive printed patient information developed by the German College of General Practitioners and Family Physicians (DEGAM) regarding blood pressure and the role of physical activity, healthy nutrition, and smoking cessation. GPs will be appealed to deliver patient information to the patients with hypertension.

GPs of the control group treat their patients as usual. They are invited to take part in the SDM training after the study.

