#### Baseline assessment

The baseline assessment includes all clinical data, socio-demographic data and prescription data. Before the ABPM will be performed, patients complete a first questionnaire including socio-demographic data, intention-to-treat-hypertension index [12], medication adherence report scale (MARS-D) [21], helping relationship in taking medication [22], Autonomy Preference Index (API) [23], Trust in Physician Scale (TPS) [24], and knowledge about hypertension (8 items; developed by our research group).

If the average blood pressure in the ABPM protocol exceeds 130/80 mmHg (24 h mean) or 135/85 mmHg (daytime mean) or 120/70 mmHg (night mean), previous blood pressure treatment is considered as ‘uncontrolled’ [1,20,28]. These patients – as well as patients with any of the above-mentioned comorbidities – remain in the study. In the following visit GPs discuss with these patients possible consequences regarding the subsequent treatment. Immediately after this baseline consultation, patients will receive a second questionnaire including the above-mentioned self-reporting instruments ‘treatment decision made to control hypertension’ (instrument 7) and SDM-Q-9 (instrument 8).

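### The multi-covariate sensitivity analysis of both co-primary endpoints adjusts for outside treatment counted over the whole study, so it can be biased for the total intervention effect and cannot serve as a robustness check

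*Protocol article*

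**What the plan says.** All references are to the protocol article.

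- **The model.** Analysis of primary and secondary endpoints states: "For the primary endpoints, an additional sensitivity analysis based on a model adjusted for the prognostic factors". The list includes "baseline values of cardiovascular risk and comorbidity" and several questionnaire scales, and closes with "an indicator for treatment outside medical practice (aggregated over the complete study period) is conducted".
- **Reuse of the list.** The same section adds an exploratory analysis in which "the influence of the prognostic factors mentioned above on the primary endpoints at baseline will be investigated".
- **Time of allocation.** Randomisation of the GP practices: "As soon as the baseline assessment has been completed, GP practices will be randomised into intervention and control group". Training follows.
- **When outside care is recorded.** Follow-up assessments T1, T2, and T3 places it in the follow-up questionnaire, which includes "tobacco consumption, height and weight, and utilisation of further health services". Baseline assessment lists the contents of the first T0 questionnaire without it. After the T0 consultation, "patients will receive a second questionnaire including the above-mentioned self-reporting instruments", and the two instruments then named are the treatment decisions (instrument 7) and the SDM-Q-9 (instrument 8). Utilisation of other services is instrument 9 under Patient self-reporting instruments.
- **The primary model.** It contains the endpoint's own baseline value, intervention by time, time, and random practice and patient effects. It has no term for outside treatment. Analysis principle commits the primary endpoints to intention to treat.

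**The concern.** A covariate can be adjusted for without disturbing the randomised comparison if allocation cannot have affected it. This indicator does not meet that condition. The training is meant to change what GP and patient decide together, and includes "introduction of a decision table listing various options to lower cardiovascular risk". It could plausibly change who seeks care elsewhere. Poor blood pressure control, or a consultation in which the patient felt left out, could also send a patient elsewhere. The indicator may thus lie on the path from training to outcome, share causes with the outcome, or be a result of it.

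Adjusting for such a variable yields something other than the total effect that intention to treat targets, and the article declares no direct or conditional effect as the aim. What is at stake is the use of the analysis: a model meant to support the primary result could agree with it, or differ from it, for reasons unrelated to whether that result is robust.

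The exploratory baseline analysis has a simpler fault of timing: it would explain a T0 or T1 value by behaviour recorded up to T3.

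**Working it through.** **Step 1: timing.** T0 assessment, then randomisation, then training, then T1, T2 and T3. The indicator is one value per patient covering the whole study, so it runs to T3. The model uses k = 1, 2, 3 for perceived participation and k = 2, 3 for systolic pressure.

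- Perceived participation, β = (β1 + β2 + β3)/3: the outcomes at T1 and T2, two of the three components, are adjusted for care reported later.
- Systolic pressure, β = (β2 + β3)/2: the outcome at T2, one of the two components, is adjusted for care reported later.

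Within the same list, cardiovascular risk and comorbidity are explicitly taken at baseline and this indicator is not.

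**Step 2: the plan's own scale.** The article gives no figure for outside treatment. Its effect-size scale comes from the power section: 788 patients, 24 per practice, ICC 0.05. Variance inflation = 1 + (24 − 1) × 0.05 = 2.15, and effective N = 788/2.15 = 366.5. At two-sided α = 0.025, the power for 0.30 SD is 73.57% against the stated 73.51%, so the plan's figure is reproduced. It is used here only to set 0.30 SD as the scale.

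**Step 3: when adjustment moves the estimate.** All inputs from here on are assumptions. Let 30% of control patients have outside treatment (M = 1), let the training lower this by d, and let M shift the outcome by b SD. With direct effect τ,

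total effect = τ − b·d, and the adjusted coefficient = τ = total + b·d.

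With no common cause, the bias is b·d. For b = ±0.3 and d = 0.05, 0.10, 0.15 it is ±0.015, ±0.030, ±0.045 SD. It is zero if d = 0 or b = 0.

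**Step 4: adding a common cause.** Simulation with 1,000,000 patients (Monte Carlo SE about 2/√1,000,000 = 0.002). The unmeasured factor has loading 0.5 on the outcome and 0.5 on the tendency not to seek outside treatment. With b from −0.3 to +0.3, d from 0.05 to 0.15, and the common cause absent or present:

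| True total effect | Range of adjusted estimate |
|---|---|
| 0.30 SD | about 0.19 to 0.34 SD |
| 0 | about −0.11 to +0.05 SD |

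With d = 0 the bias is nil in every setting.

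**Step 5: the opposite association.** True effect zero, 30% against 20% treated outside, and a positive latent correlation of 0.2 to 0.5 between seeking outside care and the outcome: the adjusted estimate is +0.033 to +0.085 SD. For systolic pressure a positive value counts against the training; for participation it counts in favour. The sign thus depends on which assumption is made.

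**Step 6: outcome driving later care.** The training has no effect of its own on outside treatment, 30% are treated overall, and the latent correlation from outcome to outside treatment is 0.2 or 0.4. A true 0.30 is estimated at 0.293 or 0.270. With a true effect of zero there is no bias.

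**The case against.** The strongest reply is that this is a secondary matter resting on a possibility. The analysis is labelled additional, the primary model omits the indicator, nothing in the plan makes the primary conclusion depend on agreement between the two, and no statement says that the training alters outside care. All of that stands, and it limits how far the point can be taken.

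A reader might go further than the documents allow in four ways:

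- **That the estimate is biased.** Only that it can be: bias is nil if neither the training nor the outcome influences outside treatment. The article supplies a plausible route, not evidence.
- **That the false-positive rate of the trial is inflated.** The 2.5% level is set for the co-primary tests. No test or level is assigned to this model.
- **That this is the only covariate-adjusted check.** The primary model already adjusts for the endpoint's baseline, a T0-baseline sensitivity model is planned for systolic pressure, and the predictive-factor models include single covariates. This is the only multi-covariate sensitivity model.
- **That the indicator is tied to dropout.** Patients who leave may have less chance of being counted, but no scoring rule is shown, so this is conjecture.

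It can also be said that the T0 questionnaire contents are introduced as inclusions and may not be exhaustive. That does not rescue the covariate: even with some T0 information, an indicator built over the whole study still contains what happened after allocation.

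**Conclusion.** The point holds, confined to the supporting analyses. By its own definition the indicator contains post-randomisation information, and for part of each co-primary endpoint it includes care reported after the outcome was measured. If the training or an earlier outcome influences outside treatment, the adjusted coefficient does not estimate the total effect.

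Neither size nor direction follows from the documents. The illustrative departures, from about −0.11 to +0.09 SD against a planning effect of 0.30 SD, rest entirely on assumed rates and associations. They show only that the distortion can be large enough to matter for a robustness check, and can go either way. Neither agreement nor disagreement of this model with the primary result should therefore be read as evidence on robustness.

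The primary model, its significance level and the power calculation are unaffected. The exploratory baseline model gives no intervention estimate, so the bias argument does not extend to it; its fault is that a later variable is used to explain an earlier value.

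**What to change.** - Delete the outside-treatment indicator from the adjusted sensitivity model and from the exploratory model of the endpoints at baseline.
- State that the additional prognostic covariates are taken from T0. Keep each endpoint's own planned baseline: T0 for perceived participation and T1 for systolic pressure. A blanket rule of T0 covariates only would remove the T1 baseline, which Study endpoints justifies separately.
- Report outside treatment descriptively by arm and visit, as a possible consequence of the training.
- If a model with the indicator is still wanted, present it separately, labelled exploratory and not an estimate of the total effect.

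This is a change of wording in the analysis plan. It needs no new data, patients or visits. The cost is the small amount of outcome variance that the indicator would have explained.
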